#### Adaption/Maintenance of Safewards

2.6.5

Staff from a range of disciplinary backgrounds and RAC homes, along with residents and family members, will be invited to participate in a workshop to develop recommendations regarding translation and expansion of Safewards in RAC homes. This will include feasible strategies/recommendations for future implementation and maintaining the Safewards programme.

### Implementation Strategies

2.7

Implementation strategies are the ‘methods or techniques used to enhance the adoption of a clinical programme or practice’ [47, p. 2] Implementation strategies will be guided by resources that are publicly available to support the implementation and evaluation of Safewards detailed on the UK Safewards site (https://www.safewards.net/) and the Victorian Safewards trial site (https://www.health.vic.gov.au/practice-and-service-quality/safewards-victoria). Specific implementation strategies to be used are described in Table 2 and listed according to results from the Expert Recommendations for Implementing Change (ERIC) study [48]. The ERIC study compiled 73 discreet implementation strategies (with definitions) to support the process of implementation itself, including the assessment of effective strategies and reporting of outcomes [48].

### Outcomes Evaluation

2.8

The RE‐AIM [41] and CFIR [42, 43] frameworks will be applied in combination to evaluate the implementation of Safewards in RAC homes. Both quantitative and qualitative data will be used in the evaluation process. RE‐AIM will be used to describe the individual and setting‐level impact of Safewards (Reach and Effectiveness) and the setting‐level factors that support successful implementation (Adoption, Implementation and Maintenance). Table 3 provides a definition of the RE‐AIM and CFIR domains, and details on how each construct is being applied in the evaluation.

An interview schedule for aged care staff and managers, based on the CFIR domains and constructs that are most relevant to this project, has been developed to elucidate the facilitators and barriers to effective implementation (Appendix S1).

### Data Collection and Analysis

2.9

Due to practical considerations and budgetary constraints, we will use routinely collected data pertaining to changes in restrictive practice use and staff well‐being. All staff will be invited to participate in staff surveys exploring their confidence to manage residents with challenging behaviours and motivation to change practice. We anticipate data saturation with participant numbers for the interviews and focus groups.

**Quantitative Data**
1.Routinely collected data pertaining to pro re nata (PRN) psychotropic medication use (from the organisation's psychotropic register where nursing staff record PRN psychotropic medication) and inappropriate restrictive practice incidents (as reported via the Serious Incident Reporting Scheme‐SIRS) will be collected by staff from the aged care organisation and forwarded to the research team for analysis. The total number of PRN psychotropic medications used and restrictive practice events on each individual resident will be calculated over three time periods, which are (1) 12 months before the implementation of the Safewards programme; (2) from start to completion of the programme (3 months) and (3) 3‐months post the completion of the programme. The average use of PRN psychotropic medications for each individual resident per time period, and the total number of restrictive practice events per individual resident per period will be calculated. The difference between the medication usage and a number of events before and after the implementation of the programme will be analysed using the analysis of variance method. The Australian Aged Care Quality & Safety Commission govern the SIRS, which aims to identify and prevent abuse and neglect among people receiving aged care. As only ‘inappropriate’ restrictive practice use is reportable to SIRS, and there is a very low reporting rate sector wide (e.g., < 200 reports of inappropriate restrictive practice use across the entire Australian RAC sector in the October–December 2023 quarter), these data are likely to be limited.2.Surveys (preimplementation and 1 month postimplementation) exploring staff confidence, motivation and uptake of nonrestrictive practices will be forwarded to all aged care staff (*n* = 200). Surveys have been adapted from the Victorian trial (Appendix S2). All data will be de‐identified. Staff will be asked to identify site location and provide a unique identifier to allow for pre‐ and postdata to be combined. Comparisons will be made pre‐ and post‐Safewards implementation. The online platform Qualtrics will be used to collect survey data.3.Routinely collected data pertaining to resident satisfaction with care and quality of life is routinely collected by the organisation for reporting purposes (https://www.qol-acc.org/). The most recent survey data available before the intervention and at the completion of implementation phase will be used for analysis.4.Routinely collected data pertaining to staff satisfaction (from a staff satisfaction survey developed by Willis Towers Watson) and staff injury (via the Injury Management platform). All data will be de‐identified by staff working in the aged care organisation. The most recent survey data available before the intervention and at the completion of implementation phase will be used for analysis.5.The Victoria Safewards fidelity scale (https://www.safewards.net/managers/evaluation-methods) will be adapted for the setting and completed by two members of the research team on completion of the implementation phase and 3 months postimplementation. The fidelity scale reports on the number and quality of interventions that have been implemented.

We will analyse the data based on the available information on PRN psychotropic mediation and restrictive practice events. No imputation method will be applied due to the high possibility of introducing bias. For all the surveys, the incomplete information will be treated with appropriate imputation techniques consistent with the scoring protocol of the respective survey.

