The Safewards programme, an evidence‐based model and set of interventions developed to reduce restrictive practices in inpatient psychiatric settings [4], offers a possible solution. Safewards has been adapted for use in a range of settings where restrictive practices are used, including emergency departments and general medical wards. This study aims to determine the feasibility of implementing Safewards in RAC homes. Approximately 191,000 people are living in RAC in Australia, with most people presenting with high care needs for cognition and behaviour (81% people living with dementia and 48% for people without dementia) [5]. Cognitive decline and changes in behaviour can result in a range of safety concerns for residents and staff. Clinical guidelines state that nonpharmacological interventions should be prioritised as the first‐option interventions for people living with behavioural and psychological symptoms of dementia [6]. However, staff in RAC report the need for restrictive practices to ensure the safety of the person, other residents, staff and visitors and to prevent falls [7, 8]. A recent scoping review of the international literature reported that 30.7%–64.8% of people living with dementia in aged care have experienced restraint use [9]. However, restrictive practices cause significant harm, including death [10]. Consequences of restraints for individuals can be physical (e.g., pressure injuries, incontinence, falls and reduced mobility) and psychosocial (e.g., anger, depression, reduced independence and social isolation) [11, 12]. Furthermore, the use of restraints can negatively impact carers' and workers' well‐being [11].

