In Australia, despite policy commitment, the acknowledged harms and multiple reviews recommending reduced reliance on restraints, restrictive practice remains prevalent in aged care homes [3]. Quality indicators for RAC in Australia report that the current rate of restraint use (including physical, mechanical and environmental restraint and seclusion) is 18.1% (a decrease of 23% from 12 months earlier) [13]. Research into restrictive practices in aged care homes shows that restraint use is influenced by a range of factors, including legislation and policy, and resident, staff and job characteristics [11]. The overuse of restraints in aged care has been found to be related to systemic issues rather than clinical needs, specifically inadequate staffing (skill mix and levels) and training [3, 8]. Proposals for reducing restrictive practice use include addressing attitudes and culture, enhancing training and education and reforming legislation and policies [14]. Several recent systematic reviews have examined interventions aimed at reducing physical restraint use in RAC [15, 16, 17]. Overall, there appears to be more evidence for multicomponent interventions (e.g., policy changes and education) rather than education alone [15, 16]. Strategies/interventions developed specifically to reduce overprescribing of psychotropic medication (a common restrictive practice) in RAC are also often multicomponent [18]. Previous studies have focused on training nursing staff and rarely include the voices of residents [15, 16]. To date, in Australia, reforms aimed at minimising restraint use have focused on amendments to legislation and policy [19, 20]. For example, aged care providers must monitor, review and report restraint use. Although providers are required to reduce restrictive practice use, there remains a gap in knowledge about the most effective strategies/interventions to achieve sustained reduction in restraint use in RAC. This study will extend current knowledge by testing a programme aimed at reducing conflict and restraint use. Training will be provided to personal care workers, who are the majority workforce in RAC in Australia, and residents will be included in the evaluation.

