In Australia, Safewards has been implemented in two states by the Departments of Health in Victoria and the ACT, with trials extending beyond adult mental health units to older person's mental health units, a general medical ward, an emergency department and an aged care residential setting [28]. All programme evaluations indicated that the implementation of Safewards was effective [28] in terms of improving seclusion rates, with the exception of aged care psychiatric units which were excluded from the analysis due to reporting zero or near zero seclusion events [29]. The recommendation from the Victorian Safewards trial in an aged care setting was that future evaluation focuses on changes in restraint use rather than seclusion rates, which is the more common practice in aged care [29]. Staff reports regarding the acceptability of the model and interventions were highly favourable, demonstrating that Safewards is an acceptable practice change intervention [28, 30]. Although Safewards has proven to be an effective programme in psychiatric settings, it is not known if it will be either effective or feasible to implement in RAC. To support and evaluate implementation, this study is informed by implementation frameworks.

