#### Evaluation Phase

2.6.4

Programme evaluation will examine the impact of Safewards in aged care homes, and identification of successful implementation strategies and adaptations made to the interventions for service fit. Further details of the outcomes evaluation are provided in Table 3.

**Table 3 hex70037-tbl-0003:** Evaluation summary.

**RE‐AIM domains**	**Evaluation aims and outcome measures**
*Reach:* Participation in the intervention (individual level)	*Aim*: To describe the number, proportion and characteristics of staff who are willing to participate in the intervention. *Data collection: Quantitative*—Number of staff who engaged in the training and participant characteristics (age, gender, qualifications and cultural background).
*Effectiveness*: Impact of the intervention (individual and setting level)	*Aim:* To determine the appropriate and feasible effectiveness outcome measures and potential signals of effect. 1. *Resident outcomes. Data collection: Quantitative*—Pre‐ and postquarterly reports of pro‐re‐nata psychotropic medication use, pre‐ and postquarterly reports of incidents of mechanical, physical and environmental restraint. *Qualitative*—Interviews postimplementation to understand the experiences of the intervention. 2. *Family member outcomes. Data collection: Qualitative*—Interviews postimplementation to understand experiences of the intervention. 3. *Staff outcomes. Data collection: Quantitative:* Pre‐ and postsurveys to assess levels of confidence and capacity to support residents with complex needs and use the intervention, pre‐ and postsurveys to assess staff well‐being. *Qualitative*—Focus groups (or interviews) to understand experiences of the intervention.
*Adoption:* Degree of uptake of intervention (individual and setting level)	*Aim:* To describe the number, proportion and representativeness of staff and settings who delivered the intervention. *Data collection: Quantitative*—Setting exclusions/inclusions (% units and reasons); staff exclusions/inclusions (% of staff invited that participate in training); degree of implementation of Safewards (number of interventions implemented). *Qualitative*—Focus groups (or interviews) to understand staff perceptions of barriers and enablers to setting‐ and staff‐level adoption.

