### Ethical Considerations

2.10

Ethics was sought from the Flinders University Human Research Ethics Committee to conduct this study. A waiver for consent was sought for de‐identified data including the following: (1) routinely collected data pertaining to psychotropic medication use and restrictive practice incidents (physical, mechanical and environmental restraint); (2) staff satisfaction surveys and (3) consumer satisfaction and quality of life questionnaires.

Data pertaining to psychotropic medication use will be collected and de‐identified by staff from the aged care organisation via an electronic record and/or the psychotropic register. Restrictive practice incidents, documented on internal incident report forms, will be collected and de‐identified by organisational staff. Anonymous staff and consumer satisfaction and quality of life surveys are routinely collected for reporting purposes.

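### The non-chemical restraint outcome has three unreconciled sources, and the one tied to the analysis would yield almost no events

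*Protocol article*

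**What the plan says.** The protocol article describes the source of the restraint data in three ways.

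- **Section 2.9, Quantitative Data, item 1.** The data are "inappropriate restrictive practice incidents (as reported via the Serious Incident Reporting Scheme" (SIRS). Events are totalled per resident over 12 months before the programme, the 3 months of implementation and the 3 months afterwards, and before is compared with after by analysis of variance. This is the only place that states how the events are counted and analysed. The same item explains that only use classed as inappropriate is reportable, says that "there is a very low reporting rate sector wide", cites fewer than "200 reports of inappropriate restrictive practice use across the entire Australian RAC sector" in one quarter, and expects the data to be limited.
- **Table 3 (section 2.6.4), Effectiveness, resident outcomes.** The measure is pre- and "postquarterly reports of incidents of mechanical, physical and environmental restraint", with no restriction to inappropriate use.
- **Section 2.10, repeated in the Ethics Statement.** "Restrictive practice incidents, documented on internal incident report forms, will be collected" and de-identified by the organisation's staff. The consent waiver sought covers physical, mechanical and environmental restraint incidents.

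Section 2.9 item 1 also analyses PRN psychotropic use, taken from the organisation's psychotropic register. That is a separate measure.

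**The concern.** The three descriptions differ in source and in what counts as an event. A SIRS report exists only when use was judged inappropriate; the Table 3 measure carries no such filter. Internal forms may feed SIRS, but the protocol does not say so. Read literally, the analysis runs on the narrowest of the three, which the protocol itself expects to be sparse.

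Two things are at stake. First, the Effectiveness aim in Table 3 is to identify feasible outcome measures and possible signals of effect, and section 2.1 says the findings will inform a future trial. A count close to zero gives no signal and no usable planning rate for non-chemical restraint. Second, while three sources remain open, the one reported could be chosen after the data are seen.

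**Working it through.** The protocol states no expected event count for this outcome, so there is no figure to reproduce. The check uses its own inputs.

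**Inputs**
- Sector reports per quarter: fewer than 200 (section 2.9), taken as an upper bound of 200.
- Sector population: "Approximately 191,000 people are living in RAC in Australia" (Introduction).
- Residents at the two homes: 115 + 76 = 191 (section 2.3).
- Windows: 12 months before, 3 during, 3 after, or 4 + 1 + 1 = 6 quarters (section 2.9).
- Assumption: the two homes report at the sector-average rate. This is varied below.

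**Expected reports**, both homes together = 200 × (191 / 191,000) × quarters = 0.2 × quarters. Under a Poisson model, P(no reports) = exp(−expected).

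| Window | Expected (at most) | P(no reports) |
|---|---|---|
| 3 months after | 0.20 | 0.82 |
| 12 months before | 0.80 | 0.45 |
| All 18 months | 1.2 | 0.30 |

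**Sensitivity to the reporting rate**

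| Multiple of sector average | Expected before | Expected after | P(none after) |
|---|---|---|---|
| 1 | 0.8 | 0.2 | 0.82 |
| 2 | 1.6 | 0.4 | 0.67 |
| 5 | 4.0 | 1.0 | 0.37 |
| 10 | 8.0 | 2.0 | 0.14 |

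**Could any result show a reduction?** Suppose there is no effect. Given the total of before and after events, each falls in the 12-month window with probability 12/15 = 0.8. The most favourable outcome is n events before and none after, with one-sided p = 0.8^n. This first drops below 0.05 at n = 14 (0.8^14 = 0.044). Ten times the sector average gives only about 8 baseline events. This test allows for the unequal windows. Analysis of variance on per-resident totals that are nearly all zero cannot recover information the counts lack.

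**The case against.** The strongest reply is that the protocol already discloses the sparsity. It gives the sector figure, explains why reporting is low, says the data will be limited, and explains in section 2.9 that routine data are used for practical and budgetary reasons. In a pilot meant partly to learn which measures are feasible, finding SIRS too thin is a legitimate result. That stands, and it lowers the severity. But the caveat neither reconciles the sources nor withdraws the analysis of variance.

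Several stronger readings are tempting but not supported:

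- **That the study's main outcome is empty.** No primary outcome is named. Effectiveness is one of five RE-AIM domains, and restraint incidents are one measure within it.
- **That the pilot can give no signal on restrictive practice.** PRN psychotropic use does not depend on SIRS, and the Introduction calls psychotropic medication a common restrictive practice. Only non-chemical restraint is affected.
- **That a better source would show about 35 restrained residents.** The Introduction says "restraint use (including physical, mechanical and environmental restraint and seclusion) is 18.1" per cent, and 0.181 × 191 ≈ 35. But that rate includes seclusion and gives a number of residents rather than of reports, so it shows scale only. It does not establish what the internal forms would yield, or that SIRS misses most of the restraint the programme targets.
- **That this repeats an earlier failure.** The units the Introduction describes as excluded were aged care psychiatric units with zero or near-zero seclusion. The advice that "future evaluation focuses on changes in restraint use rather than seclusion rates" agrees with Table 3. It is an analogy, not a precedent for SIRS.

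The homes may also differ from the sector average: 8 + 9 + 9 + 15 + 9 = 50 of the 191 residents live in specialist dementia or memory support units. The tenfold row allows for a large difference and the conclusion does not change.

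**Conclusion.** The concern holds for the non-chemical restraint outcome. Table 3, section 2.9, section 2.10 and the Ethics Statement give three sources and at least two event definitions, with nothing linking them. If section 2.9 is followed as written, SIRS would supply at most about 0.2 reports in the post period and 1.2 over 18 months at the sector-average rate, and about 2 in the post period at ten times that rate. The planned comparison could not show a signal. The size rests on the protocol's sector figures, the assumed rate multiples and a Poisson model; the inconsistency rests on the text alone.

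This should be fixed but does not invalidate the study: it is a two-site pilot with no named primary outcome, a disclosed limitation and a separate PRN psychotropic measure.

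**What to change.** Align Table 3, section 2.9 item 1, section 2.10 and the Ethics Statement as follows:

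1. **One event definition:** any mechanical, physical or environmental restraint incident.
2. **One source in every period:** the internal incident report forms. First confirm with the organisation that they give resident-level counts for all three windows. If they do not, report site-level quarterly counts instead.
3. **SIRS as a descriptive count only,** outside the analysis of variance.

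The cost is mainly wording plus that one check, since collection of the forms is already planned and falls within the waiver sought. There are two downsides. The documents do not give the yield or completeness of the forms, so they may also under-record. Training may change how staff report incidents, so a change in counts could reflect reporting rather than practice; this should be noted in the interpretation.

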#### Implementation Phase

2.6.3

Implementation of Safewards at each site will occur over 12 weeks. The clinical educator from the aged care organisation and two trainers from the project team (one staff with lived experience of caring for a family member with dementia) will provide on‐site training of aged care staff. An online community of practice groups will be established to share learnings and support implementation across sites.

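### A whole-year baseline is set against 3-month windows, so any yearly cycle in PRN psychotropic use would enter the before-after difference even on a per-resident-day scale; a same-calendar-month sensitivity comparison would show it

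*Protocol article*

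**What the plan says.** Section 2.9, Quantitative Data item 1, fixes three periods for the routinely collected resident data: the "12 months before the implementation of the Safewards programme", the span "from start to completion of the programme (3 months"), and a further 3 "months post the completion of the programme". Section 2.6.3 is consistent on the programme's length: "Implementation of Safewards at each site will occur over 12 weeks".

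Each period is reduced to one number per resident. For medication this is "The average use of PRN psychotropic medications for each individual resident per time period"; for restraint, "the total number of restrictive practice events per individual resident per period will be calculated". Then "The difference between the medication usage and a number of events before and after the implementation of the programme will be analysed" by analysis of variance. The text mentions no calendar matching, seasonal term or monthly series.

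Four other places bear on the point:

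- Section 2.3 names two homes, and no concurrent control is described anywhere.
- Table 3 (Effectiveness) gives the aim as finding feasible measures and possible signals of effect, and refers to quarterly reports before and after.
- Section 3.3 lists the 12-month project timeframe and sector reform as limitations, but not season.
- No calendar start date is given.

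**The concern.** A 12-month window averages over every part of the year. A 3-month window sees only one quarter of it, so only 3/12 = 25% of the baseline falls in the same calendar months as either later window. If PRN use follows a yearly pattern, for instance through staffing, leave or outbreaks, a window in a low quarter looks like a reduction and one in a high quarter looks like an increase, whatever the programme does.

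This is separate from the unequal length of the windows. Dividing by resident-days corrects the 12:3 imbalance in exposure but leaves the imbalance in calendar coverage. With no concurrent control described, the choice of comparison months is one of the few protections available.

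What is at stake is the planning of the later trial. Section 2.1 says the findings will inform it, and a calendar artefact in the PRN result could be carried forward as an early signal or a planning effect size.

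**Working it through.** The plan states no seasonal figure, effect size or power calculation, so there is no figure of its own to reproduce. The check asks how large an apparent change can arise with no programme effect and rates already on equal time.

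**Inputs from section 2.9.** Baseline: months -12 to 0. Period 2: months 0 to 3. Period 3: months 3 to 6. (The 12 weeks of section 2.6.3 are 84 days, close enough to 3 months.)

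**Assumption.** Monthly rate = 1 + a·cos(2πt/12). The amplitude a is not in the documents, so a range is shown.

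**Bias against the full baseline.** The baseline mean is exactly 1, because a full cycle averages out. The largest deviation of a 3-month mean from 1 is a·sin(π/4)/(π/4) = a·0.7071/0.7854 = 0.90a. The average absolute deviation over all start dates is 0.90a·(2/π) = 0.57a.

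| Assumed amplitude a | Lowest to highest apparent rate ratio | Average absolute bias |
|---|---|---|
| 5% | 0.955 to 1.045 | 0.029 |
| 10% | 0.91 to 1.09 | 0.057 |
| 20% | 0.82 to 1.18 | 0.115 |
| 30% | 0.73 to 1.27 | 0.172 |

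The ranges are the same for periods 2 and 3. The bias is near zero when the window is centred where the cycle crosses its yearly mean.

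**A different shape.** If one quarter is 20% higher and the others are flat, the yearly mean is (1 + 1 + 1.2 + 1)/4 = 1.05. A window in the raised quarter shows 1.2/1.05 = 1.14; a window in any other shows 1/1.05 = 0.95.

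**Same calendar months.** Twelve months before period 2 is months -12 to -9; twelve months before period 3 is months -9 to -6. Both lie inside the planned baseline. Under the cosine model the matched ratio is 1.000 for every start date and amplitude. This removes only a pattern that repeats from year to year.

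**The cost of matching: secular trend.** The Introduction reports a 23% fall in restraint use over 12 months. That indicator covers physical, mechanical and environmental restraint and seclusion, not PRN medication, so it serves here only as an illustrative drift rate of 0.77 per year. The baseline midpoint is month -6.

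| Window | Midpoint | Gap to full baseline | Drift, full baseline | Drift, matched (12-month gap) |
|---|---|---|---|---|
| Period 2 | +1.5 | 7.5 months | 1 - 0.77^(7.5/12) = 15% | 23% |
| Period 3 | +4.5 | 10.5 months | 1 - 0.77^(10.5/12) = 20% | 23% |

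**Which outcome it applies to.** Section 2.9 gives fewer than 200 SIRS reports of inappropriate restrictive practice sector-wide in one quarter. The Introduction gives about 191,000 residents, and section 2.3 gives 115 + 76 = 191 at the two sites. At the sector rate that is fewer than 200 × 191/191,000 = 0.2 reports per quarter in both homes together. A matched-quarter comparison of SIRS events would usually be zero against zero, so the point concerns PRN use.

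**The case against.** The strongest reply is that the premise has no support in the documents. Nothing says that PRN use is seasonal, no start month is given, and 9% and 18% are worst-case values for assumed cycles. That stands: size, direction and even existence of the bias are unknown.

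A second reply is that a same-month sensitivity analysis is the sort of detail left to an analysis plan, and that the quarterly reports in Table 3 suggest the data could support one. This stands in part. The 12-month baseline is not wrong and should stay. But section 2.9 does fix the periods, the one-number summaries and the method, and as fixed they carry the imbalance.

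Third, matching increases exposure to a steady decline, and decline over time is the only time pattern the documents report. That is correct, and the added cost is larger for period 2 than for period 3. It limits matching to a supporting role.

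Three stronger readings are tempting and are not supported:

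- A reader might infer that every resident in both homes receives the programme, so that no internal contrast can exist. The article does not say so; under Adoption, Table 3 plans to record which units are included or excluded. It can be said only that no concurrent control is described.
- A reader might infer that the change from period 2 to period 3 is a planned test of persistence and is distorted by season. Section 2.9 specifies a before-after comparison only, and Table 3 assesses Maintenance by fidelity checklist, surveys and focus groups.
- A reader might conclude that a reduction should count only if the full-baseline and matched comparisons agree. With SIRS counts this sparse, such a rule could seldom be applied.

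**Conclusion.** The point holds in conditional form. As written, the comparison sets a whole-year average against quarter-year windows with no concurrent control described, and conversion to rates does not cure this. If PRN use has a stable yearly cycle, the before-after difference carries a calendar component of up to 0.90 times its amplitude. Both the cosine shape and the amplitudes behind the 9% and 18% figures are assumptions.

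The severity is low. The study is a pilot, and effectiveness is left to a later trial. The documents do not show that the PRN result will be biased, only that the plan as stated could not tell a yearly cycle from a programme effect.

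**What to change.** In section 2.9, item 1:

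1. Keep the 12-month baseline as the main comparison and express it per resident-day.
2. For PRN psychotropic use, add a sensitivity comparison with the same calendar months one year earlier, counted from programme start: period 2 against months -12 to -9, and period 3 against months -9 to -6.
3. Plot monthly PRN rates over all 18 months, so that season and trend can both be seen.
4. Report whether the full-baseline and matched comparisons agree, and treat a signal seen in only one with caution. Do not impose a strict agreement rule.
5. For SIRS events, show counts by period only.

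The cost is a few lines of analysis with no new participants. It assumes that the register extract carries dates at least to the month. If only quarterly reports are available, matching works only where reporting quarters line up with programme start, and the plot becomes quarterly.

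The downside is that each matched quarter uses a quarter of the baseline data and, at the illustrative decline rate, carries more drift than the full baseline for both windows. The matched comparison should therefore be labelled as supporting and should not replace the main one.
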